## Abstract

**Background:**

Acute herpes zoster (AHZ) is a common skin disease caused by invasion of the varicella zoster virus into the ganglia and skin, and the severe pain is the most complaint, which can seriously disturb the normal life of patients. Fire needle plus cupping is a special acupuncture treatment, which is widely used to treat AHZ for its better analgesic effect in China although it has not been fully verified by rigorous randomized controlled trial (RCT).

**Methods/design:**

To test the effect, a three-arm randomized parallel controlled trial protocol has been designed. A total of 105 AHZ patients suffering pain will be randomly divided into three groups in an equal proportion. The interventions are fire needle plus cupping (FC) in group A, famciclovir plus gabapentin (FG) in group B, and fire needle plus cupping plus famciclovir (FCF) in group C. The length for the trial is set for a week time frame. Precisely speaking, the A group (FC) is to carry out 1 treatment per day for the total of 7 treatment sessions within 1 week period. On the other hand, the B group (FG) will take drugs orally three times a day within the trial 1 week. Meanwhile, with its combination element, the C group (FCF) is due to undertake both treatments and drugs as prescribed for A and B groups within the trial week. As an intra-trial arrangement, analgesic medication will be carefully administered for temporary pain release if the sudden intolerable pain appeared. For the primary outcome, this study is due to apply visual analogue scale to identify pain intensity relief. As the secondary outcomes are concerned, this study is aiming to focus on the issues related to changes in substance P and beta-endorphin concentrations in peripheral plasma, as well as those issues of analgesic needs, side effects, symptoms, and physical signs including pain classification, local itching, burning sensation, fever, local lymphadenopathy, skin lesion area, blisters, herpes clusters, vesicular traits, ulcers, and pimples; all these are taken into account for evaluation. For the final stage, the participants are to be followed up for postherpetic neuralgia.

**Discussion:**

The results of this trial aim to provide sufficient evidence on FC treatment over both FG and FCF treatments. It will then give a credible alternative treatment to cut down acute pain and to cure AHZ infection.

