## Methods

### Objective

The main purpose of this trial is to gather evidence for the designed treatment in group A (FC) and investigate the effect of designed treatment on relieving the *acute* pain phase in AHZ. Another objective would also be to analyze the correlation between the concentration of substance P and β-endorphin (®-Ep) in peripheral plasma and changes in pain intensity by FC intervention.

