### Intervention

#### Group A

This group will be treated with only FC.
Acupoints: the main points are Ashi points (lesion area), corresponding nerve segment Jiaji points, and branch ditch points (SJ6); matching points are selected according to syndrome differentiation, pattern of dampness-heat in the liver meridian with Yang Ling Quan (GB34), pattern of dampness-heat in the spleen meridian with Yin Ling Quan (SP9), and pattern of obstruction of collaterals by blood stasis with blood sea (SP10).Appliances: medium-sized fire needle (diameter 0.4 mm), large-sized fire needle (diameter 0.65 mm), glass fire cup no. 1–5, medical cotton ball, alcohol lamp, lighter, iodophor, etc.Operational methods: routine disinfection of the skin with iodophor with the order of the head, middle, and tail of herpes will be carried out firstly. Holding 95% alcohol lamp by the left hand close to the needle, and to burn the needle in the right hand to whitening by the external flame of the fire, acupuncturist will prick the head of the herpes cluster. Then, the needles will be pricked into the blisters or rashes quickly from the surface of the skin to the base of the herpes. Pricking early-onset herpes at first, for larger pustules or blood blisters (diameter ε0.5 cm) with a large-scale fire, acupuncturist will extrude blister fluid with disinfection cotton ball after puncture, and then cup with a suitable size of glass fire cup for 5–10 min. If the area of the herpes cluster is too large, more than one cup can be used. The remaining acupuncture points are treated with fire needle pricking, and each acupuncture point should be pricked three times. Finally, the skin should be sterilized with iodophor more than one time. The treatment should be performed once a day for a total of 7 days.Skin care: after treatment, the iodophor is used to clean and disinfect the skin and to keep the patient’s skin dry and clean during the treatment.Course of treatment: the course of treatment is 1 week and from one to seven times. If there is no pain any more after one time of FC treatment, the course is just one time. Meanwhile, if the patient is still suffering pain, the FC will continue once a day unless the pain disappears. All the treatments will not be more than seven times no matter the pain or not.

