#### Follow-up

To evaluate the incidence of postherpetic neuralgia symptom, a follow-up call is designed and recorded 6 months later posted after the end of the 1-week treatment. (Table 2).

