### Outcomes

#### Primary outcome

The primary outcome has been the changes in pain intensity pre- and post-treatment (VAS 0–100 mm, where 0 = *painless* and 100 = *maximum imaginable pain*).

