#### Secondary outcomes

First of all, pre- and post-treatment periods, the plasma of the participants is carefully collected and centrifuged and stored in a − 80 °C refrigerator. It is then the substance P and ®-Ep in serum can be detected by an enzyme-linked immunosorbent assay. Quantitative scoring methods have been further applied to evaluate the symptoms and physical signs before and after treatment, including pain intensity, local itching, burning sensation, rash color, numbers of blisters, clusters, ulcers, fever, local lymphadenopathy, and rash area (Table 2).

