## Discussion

This study is a randomized controlled clinical trial with the grouping comparison of FC, FG, and FCF. To our knowledge, so far, this study may be the first clinical trial study that aims to demonstrate the FC effect on AHZ infection with rigorous design and it may also be different from the reference therapy. However, it has gotten our attention that several existing Chinese literatures did report on fire needle and cupping technique to cure for HZ [12–14, 16] but all of them did not take up a rigorous design trial and are lacking of sufficient evidence to prove FC treatment has a positive effect on AHZ.

The key objective of this study is to test the three designed treatment groups on the analgesic effect in acute phase of AHZ disease. We will also pay great attention to the observation of the scores of skin lesions, since skin rash is also the deep concern of patients. We also want to detect variation in serum due to the fact that the substance P and ®-Ep are often regarded as the analgesic mechanism. In addition, the occurrence of postherpetic neuralgia may need to be carefully observed and examined due to its common occurrence and hard to cure nature in AHZ infection. The symptom of acute pain is what the AHZ patients want to solve mostly and cannot approve to participate in an invalid treatment group.

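### The abstract promises a cure and the sample size rests on cure rates, but no listed outcome defines cure or measures viral clearance

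*Protocol article*

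**What the plan says.** All references are to the protocol article.

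- **Abstract, Discussion.** The stated expectation from the results is: "It will then give a credible alternative treatment to cut down acute pain and to cure AHZ infection".
- **Objective.** The main purpose is to gather evidence on FC and "investigate the effect of designed treatment on relieving the" acute pain phase. Cure is not mentioned.
- **Discussion (main text).** "The key objective of this study is to test the three designed treatment groups on the analgesic effect in acute phase of AHZ disease".
- **Primary outcome.** "The primary outcome has been the changes in pain intensity pre- and post-treatment", on a 0–100 mm VAS.
- **Secondary outcomes and Table 2.** Ten symptoms and signs are scored before and after treatment. Besides pain, itching and burning, they cover the rash, blisters, clusters, ulcers, fever and lymph nodes. On the laboratory side, "substance P and ®-Ep in serum can be detected by an enzyme-linked immunosorbent assay". No viral measure is listed.
- **Follow-up.** "To evaluate the incidence of postherpetic neuralgia symptom, a follow-up call is designed and recorded 6 months later".
- **Group A.** "This group will be treated with only FC". Group B receives famciclovir plus gabapentin (FG). Group C receives the same FC as group A plus famciclovir (FCF).
- **Sample size estimation.** Cure rates of 37.8% (famciclovir), 76.4% (FC) and a speculated 80.0% (FCF) enter an arcsine formula, giving 32 per group, 96 in all, and 105 with dropout. Cure is not defined there.

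**The concern.** The document uses cure in two places that matter: the conclusion it expects to draw and the effect size that fixes the number of patients. The outcomes section, which should connect the two, has no cure outcome.

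The first consequence concerns the conclusion. If the plan is followed exactly, the claim about cure will have no predefined outcome behind it, and a favourable VAS difference could be reported under a sentence that also speaks of curing the disease. The second concerns the sample size. The 90% power that the plan states refers to a quantity the trial does not list, and says nothing direct about the VAS comparison that is the declared primary outcome.

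**Working it through.** **1. Reproduce the plan's own figure.** Inputs from Sample size estimation: P_max = 0.80, P_min = 0.378, two-sided alpha 0.05, beta 0.1. The article does not print lambda. I assume the noncentral chi-square parameter for three groups (2 degrees of freedom), which is 12.654.

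- Arcsine difference: 2·asin√0.80 − 2·asin√0.378 = 0.8900
- n = 2λ / difference² = 2 × 12.654 / 0.8900² = 31.95, rounded up to 32 per group
- 3 × 32 = 96, and 96 × 1.09375 = 105

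With 1 degree of freedom (lambda 10.507) the result would be 26.53, so 27. The stated 32 is therefore the three-group calculation on cure rates, done correctly.

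**2. Look for the outcome those rates belong to.**

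| Place | What it concerns | Defines cure or viral clearance? |
|---|---|---|
| Objective | Acute pain; correlation of two plasma markers with pain | No |
| Primary outcome | VAS change | No |
| Secondary outcomes, laboratory | Substance P, beta-endorphin | No |
| Secondary outcomes, Table 2 | Graded symptoms and signs | No threshold or combination named |
| Table 2, other entries | Analgesic demand, side effects | No |
| Follow-up | Postherpetic neuralgia at 6 months | No |
| Sample size estimation | Cure rates | Uses the term, does not define it |
| Abstract, Discussion | Cure as an expected conclusion | Uses the term, does not define it |

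**3. Can Table 2 supply a cure definition as it stands?** Not yet.

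- Rash area reduction scores 0 for no reduction and 3 for 100%, so a high score is good. In the other rows a high score is bad.
- The same row has categories below 30%, below 60% and 100%. A reduction from 60% to just under 100% has no score.
- Blister count goes from 11–15 (2 points) to above 26 (3 points), so 16 to 26 has no score.
- Blister clusters are 3–4 (2 points) and 4–5 (3 points), so four clusters fit both.

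**4. What 32 per group gives for each kind of outcome.** If cure were defined and the stated rates held, with the famciclovir rate standing for group B, power at two-sided 0.05 would be about 90% for FC against FG (76.4% v 37.8%) and about 5% for FC against FCF (76.4% v 80.0%). At a Bonferroni level of 0.05/3 the first falls to 78%.

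For a pairwise VAS comparison by normal approximation, the standardised difference detectable with 90% power is (1.960 + 1.282) × √(2/32) = 0.81 SD, or 0.92 SD at 0.05/3. The article gives no VAS standard deviation, so this cannot be turned into millimetres.

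**The case against.** **The trial measures more than pain.** A reader might infer from the mismatch that the trial yields only a one-week pain result. It does not. Rash, blisters, ulcers, fever and lymph nodes are prespecified, the Discussion stresses lesion scores, and postherpetic neuralgia is followed up at 6 months. This stands. A difference in complete clearing of lesions would bear on clinical resolution, though not on viral clearance.

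**The antiviral-free arm is not the fault.** A reader might also infer that cure cannot be shown because group A receives no antiviral. The documents do not support that. An arm with FC alone is what would let an effect be attributed to FC if cure were measured; what is missing is the endpoint. Nor is a blanket statement warranted that the trial says nothing about doing without the antiviral. Groups A and C differ by design only in famciclovir, and the Discussion gives this contrast that purpose. It does bear on what famciclovir adds for the measured outcomes, however weak its power.

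**Infection is used loosely.** The article often writes infection where it means the disease, so the abstract may intend no more than resolution of zoster. That is fair and weakens a strictly virological reading. It does not supply a definition of resolution either.

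**It is one hopeful sentence, and the full protocol may define cure.** No test depends on the abstract's wording, and the closing conclusion of the main text is more guarded. But the sample size does depend on cure rates, so cure is not just a turn of phrase. The point also does not rest on omitted detail: the article lists its outcomes and states a conclusion and a sample size basis that they do not match. If the full protocol does define cure, naming that outcome in the article would settle most of the matter.

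**Conclusion.** The concern holds in this form: the article expects to conclude on cure and sizes the trial on cure, but none of its listed outcomes defines cure or measures viral clearance. The scored signs allow a limited statement on clinical signs and no more.

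In size, this is a fault of claim and endpoint, not of arithmetic. The figures of 32, 96 and 105 are reproduced and need not change. What changes is what they mean: the stated 90% power belongs to an unlisted cure outcome, while for a pairwise VAS comparison the same 32 per group corresponds to a detectable difference of 0.81 SD unadjusted. The conclusion assumes that the outcomes printed in the article are the complete list; the reproduction of 32 also assumes the three-group lambda, which the article does not print.

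**What to change.** Take one of two routes.

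1. **Narrow the claim.** In the abstract's Discussion, limit the expected conclusion to relief of acute pain at the end of the treatment week, plus the scored clinical signs. In Sample size estimation, add that the number was derived from published and speculated cure rates and not from the VAS primary outcome. Changing the abstract alone is not enough, because the sample size would still rest on an outcome found nowhere else.
2. **Define cure.** Add a secondary outcome at the end of treatment, built from signs already scored, with its components and thresholds stated. First make the Table 2 categories complete, non-overlapping and consistent in direction. Compare the proportion cured between groups and label the analysis exploratory. The abstract should then refer to clinical cure as so defined, not to clearance of the virus.

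The first route costs a narrower claim and two sentences. The second costs a repaired table and one extra exploratory analysis. Neither needs more patients, visits or assays.

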**Trial registration:**

Chinese Clinical Trial Registry ChiCTR1800015372. Registered on 28 March 2018.

## Background

Herpes zoster (HZ) is a skin infection disease caused by reactivation of varicella zoster virus which is latent in the sensory ganglia, in which a typical feature is that it causes herpes along the sensory nerve in the corresponding segment, accompanied by severe neuralgia, and a serious impact on the quality of life of patients [1]. Pain symptom is the most common in early stage of disease and many of them without visible herpes appearance. As such, it is easy to be misdiagnosed for other diseases, for example, misdiagnosis of cervical spondylosis or lumbar disc herniation when pain symptom occurs on the neck and shoulders. Another misdiagnosed case example is associated with heart-related disease if the HZ symptom appeared on the left chest. All these misdiagnosed cases are not rare of ordinary occurrences [1]. HZ can occur at any age, but elderly population seems to be most commonly affected. Epidemiological study shows that the incidence, complications, hospitalization rate, and average cost of HZ in China are climbing rapidly with the age increasing [2]. The cumulative incidence with HZ infection is 22.6/1000 among people aged over 50 years old, and this rate climbs up to 3.34 times more among the age group of over 80 years old [2].

The conventional drug therapies for HZ infection can be seen in two phases. Those in acute phase are mainly antiviral, nutritional nerve, and analgesic [3] types of drugs. The antiviral drugs are mainly oral famciclovir and valacyclovir. The nutritional nerve drug is mainly mecobalamin, and the pain relief drugs are mainly paracetamol, tramadol, dezocine, morphine, and gabapentin. However, upon an individual’s health condition, glucocorticoid drugs may be administered orally or intravenously. As in the sequelae phase, treatment drugs are mainly analgesic and antianxiety, and the oral drugs include tricyclic antidepressants, strong opioids, gabapentin, tramadol, and pregabalin. In addition, the drugs such as methylprednisolone and triamcinolone acetonide can be used as nerve-blocking therapy. All of these abovementioned conventional drug schemes yield potential side effects, and it is especially for patients with renal insufficiency or immune system diseases as for these patients the abovementioned schemes are difficult to implement [3]. Furthermore, the cumulative medical cost is high for such treatments on this disease, and patients are not fully satisfied even with the curative effect. With all these downsides of conventional drug therapies, it is said to believe complementary and alternative medicine such as acupuncture may give better results with less side effects and reduce medical costs to treat HZ infection [3, 4]..

Although HZ infection is not a lifelong disease, patients still suffer deeply with excruciating pain, yet it requires faster, economical, and effective treatments to relieve pain and shorter treatment courses. Acupuncture treatment has a positive therapeutic effect on pathological neuralgia, and a number of analgesic mechanisms have also been identified [5–9]. Fire needle and cupping are both traditional methods in acupuncture treatment, and its history can be rooted in many ancient Chinese literatures. The fire needle treatment is to use the alcohol lamp to burn the tip point of the special needle, and then, the needle will be pierced into and pull out the meridian or acupoint quickly—these two steps can yield both ordinary acupuncture and warming effects. When the needle operation is completed, the third step of cupping therapy is implemented immediately. This combining three-step therapy is widely used in the treatment of acute pain symptoms of HZ infection in Chinese hospitals nationwide; however, the test of efficacy of this treatment has not been performed under rigorous RCTs [10–12].

Evidently, by several decades of current and ancient traditional Chinese medicine (TCM) practitioners as well as literatures of TCM, the treatment of fire needle plus cupping (FC) has a positive effect to promote qi and activate blood circulation, which then in turn could increase the nutrition around the lesion and promotes tissue regeneration, and resulting in natural wound healing. Ancient TCM practitioners also found that the heat provided by fire needles can promote microcirculation in the lesion area through the regulation of cutaneous nerves, and it is particularly beneficial to the absorption of inflammation and metabolites [13]. Furthermore, the high temperature of fire needles can generate an effect that directly kills the microorganisms and achieves anti-inflammatory outcomes [14]. Therefore, this trial is aiming along the same line as ancient TCM practitioners and to further provide the fact results in order to validate the analgesic effect on acute herpes zoster (AHZ) treated by trial group A (FC).

## Methods

### Objective

The main purpose of this trial is to gather evidence for the designed treatment in group A (FC) and investigate the effect of designed treatment on relieving the *acute* pain phase in AHZ. Another objective would also be to analyze the correlation between the concentration of substance P and β-endorphin (®-Ep) in peripheral plasma and changes in pain intensity by FC intervention.

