#### Mechanism of fire needle cupping

Based on the theory of traditional Chinese medicine, the main causes of herpes zoster are dampness and heat, which could block the meridians and collaterals, and then led to the stagnation of blood and Qi, and finally, the pain is generated. FC has a strong effect to eliminate the dampness and heat, and make the Qi and blood smooth running, and then, the pain will be alleviated. Previous studies hint that FC can accelerate crusting and shedding of herpes, and also adjust the concentration of substance P in serum [11, 12].

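### The correlation of substance P and β-endorphin with pain change under fire needle cupping does not use randomisation, so it cannot by itself show that the treatment acts on or through these markers

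*Protocol article*

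**What the plan says.** The Objective section sets a second aim beside pain relief: to "analyze the correlation between the concentration of substance P and β-endorphin" "in peripheral plasma and changes in pain intensity by FC intervention". It names no comparator arm for this aim.

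Two other places show why the markers matter. The section on the mechanism of fire needle cupping reports that earlier studies hint that FC can "also adjust the concentration of substance P in serum". The Discussion says that "the substance P and ®-Ep are often regarded as the analgesic mechanism".

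The Secondary outcomes section sets the sampling: "pre- and post-treatment periods, the plasma of the participants is carefully collected and centrifuged". It does not restrict this to one arm. The Abstract lists changes in both marker concentrations as secondary outcomes. The Statistical analysis section plans between-group t tests with Bonferroni correction for measurement data. It describes no correlation analysis and does not refer back to the marker objective.

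**The concern.** The objective is a within-treatment association, while the interest behind it is causal: whether FC relieves pain by way of these markers. Randomisation protects a comparison between arms. It does not protect a correlation among patients who all received FC.

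The protocol supplies several influences that could move pain and markers together:

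- The Discussion acknowledges that immunity differs between patients and affects recovery and prognosis.
- The Temporary analgesics section allows rescue drugs in all groups according to pain score.
- The Group A section lets the number of FC sessions vary from one to seven according to whether pain persists, so exposure itself follows pain.

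At stake is the reading of a secondary result. A significant correlation could be reported as support for an FC mechanism when patients who recover faster would show it anyway. Conversely, a real effect of FC on the markers could go unnoticed if the correlation were the only thing examined.

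**Working it through.** **Inputs from the protocol article.** 32 per group before dropout and 105 in total in equal proportion, so 105/3 = 35 per group; two-sided alpha 0.05. The article states no expected correlation and no sample size for this objective.

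**The plan's own figure.** With the article's arcsine formula, λ = 12.654 (noncentral chi-square, 2 df, alpha 0.05, power 0.90) and an arcsine difference of 0.8900 between 0.80 and 0.378, n = 2 × 12.654 / 0.8900² = 31.95, so 32 per group. This reproduces. It is sized for cure rates, and serves here only to fix the number of patients in an arm.

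**Threshold for significance.** The critical value is |r| = t / √(t² + n − 2). For n = 35, t = 2.0345 on 33 df gives 0.334. For n = 32, t = 2.0423 on 30 df gives 0.349.

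**Shared recovery, no treatment effect.** Let R be a patient's recovery speed, standardised, and s the share of between-patient variance it explains in each measure:

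- pain change = √s · R + √(1 − s) · e₁
- marker change = √s · R + √(1 − s) · e₂

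with e₁ and e₂ independent. The pain–marker correlation is then s, and FC affects neither measure. The values of s are assumptions shown as a range. Proportion of 20,000 simulated arms in which one marker is significant:

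| Assumed correlation | n = 32 | n = 35 |
|---|---|---|
| 0 | 5% | 5% |
| 0.2 | 20% | 22% |
| 0.3 | 39% | 42% |
| 0.4 | 65% | 68% |
| 0.5 | 85% | 88% |

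**The randomised comparison under the same condition.** With no treatment effect, a between-arm t test of marker change rejects in about 5% (4.9% at n = 32 with s = 0.5; 4.8% at n = 35).

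**The opposite failure.** Set s = 0 and let treatment shift pain and marker by the same constant in every patient. The within-arm correlation averages 0.00 and is significant in 5%. A real effect on both measures leaves no trace in it.

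**Precision.** By Fisher's z, the 95% interval is tanh(atanh r ± 1.96/√(n − 3)). An observed r of 0.4 at n = 32 gives tanh(0.424 ± 0.364), or 0.06 to 0.66. Pooling A and C (n = 64) narrows this to 0.17 to 0.59. The shared influences remain, because both groups receive FC.

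**The case against.** The strongest reply is that the Objective section promises only a correlation. It does not use the word mechanism there and nowhere says the correlation will prove one. This stands: the mechanistic purpose has to be read from the mechanism section and the Discussion, and the Discussion ties it to detecting variation in the markers, not to the correlation.

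Second, the between-arm comparison is largely planned already. The Abstract, Secondary outcomes and Statistical analysis sections together cover an unadjusted comparison of the markers between groups. This also stands. What is missing is the link from the objective to that comparison, and the baseline adjustment.

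Third, a reader might infer that ordinary recovery would produce the correlation in any arm. The documents do not support that. Recovery must differ between patients and must move both measures; recovery identical in everyone gives a correlation of zero. The Background remark that "HZ infection is not a lifelong disease" does not establish recovery within one week, and the Discussion says acute pain tends to grow as the disease develops. The supportable statement is that shared influences can produce it.

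Fourth, a reader might take the 20% to 88% figures as false-positive rates. In those scenarios a correlation does exist and the test correctly finds it. They would be false positives only for a claim of mechanism, which the objective does not make.

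Fifth, the phrase "and changes in pain intensity by FC intervention" need not mean group A alone, since group C also receives FC. Including C does not change the conclusion. Leaving the details of a correlation to a fuller document is normal and is not the criticism here.

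**Conclusion.** The point holds in a limited form. A marker–pain correlation among FC-treated patients cannot by itself show that FC acts on or through substance P or β-endorphin. It can appear with no FC effect and can be absent when there is one. How often it would appear depends wholly on an unknown correlation: at 32 to 35 patients, from about 20% to 22% of trials at 0.2 to about 85% to 88% at 0.5.

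The conclusion rests on two readings: that the markers are of interest as a mechanism, which the mechanism section and Discussion support, and that plasma is taken in all arms, which the sampling text implies by not restricting it.

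It would go too far to say that the protocol claims to prove mediation, or that it ignores the control arms' marker data. No figure in the plan is wrong, and the primary pain comparison and sample size are untouched. This is a worthwhile improvement to a secondary objective.

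**What to change.** Amend the Objective and Statistical analysis sections as follows.

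1. State that the effect of FC on substance P and β-endorphin is judged by the randomised between-arm comparison of marker change, A v B, adjusted for the baseline marker: marker change = β₀ + β₁ · arm + β₂ · baseline marker, with β₁ and its 95% confidence interval reported.
2. Report the association of marker change with VAS change in all three arms side by side, with 95% confidence intervals. Use change on both sides, so that the objective, which speaks of concentration, matches the Abstract, which speaks of changes in concentration.
3. Do not treat an arm-by-marker interaction as a test of mechanism. If FC lowered a marker and pain followed it with the same slope in every arm, the interaction would be zero although the marker carried the effect.
4. Describe any correlation as an association only.

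The cost is a few sentences and a small amount of extra modelling on samples already planned, with no added patients, visits or assays. The downside is a more modest conclusion. Slopes are imprecise with 32 to 35 per arm. All arms are active, so A v B is FC against drugs. A between-arm marker difference would show that the treatments move the marker differently, but still would not prove that pain relief runs through it.
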